#### 11.3.2 Sleep Intervention

The primary outcome is CSHQ score at 3 months. Assuming that the mean CSHQ score in the 'no sleep intervention' group is 48.25 (31), a reduction to 41.1 (difference of 7.15) to be in line with normal controls (31) would require 38 per group with 90% power (assuming SD=8.9 (31).

Recognising that we might not reduce the score to be completely in line with healthy controls 50 per group would be required to have 90% power to detect a reduction to 42 (assuming SD=8.9) (31).

#### 11.3.3 Feasibility (attaining recruitment targets)

We will recruit 330 participants in total. This will give 80% power to address the aims of the drug intervention component and over 90% power to address the aims of the sleep intervention component.

### 11.4 Interim Monitoring and Analyses

We plan to undertake an internal "pilot" trial to assess recruitment and consent during the first 9 months of recruitment. The IDSMC will review the internal pilot data and make recommendations to the TSC in respect of trial continuation and possible adjusting methods for recruitment and follow-up optimisation for the remaining timeline. By the end of month 9 we expect to have opened all 22 centres and randomised 28 participants (accounting for a staggered opening of centres using a similar pattern to SANAD-II (EudraCT number 2012-001884-64)). The following criteria will be considered:

- If recruitment is 80-100% of the planned recruitment figure (28 participants), the trial will progress.

- If recruitment is 50-79% of the planned figure, the trial will progress following review of screening logs and protocol and once barriers to achieve adequate recruitment are addressed.
- Should recruitment be <50%, it is not expected the trial will progress; the decision will be made by the TSC in conjunction with the co-sponsors.

We will also assess follow-up rate, treatment failure rate, and completeness of data for primary outcomes. Although the primary aim of the trial is to compare treatment policies as applied in clinical practice (and hence an intention to treat (ITT) analysis), we will be particularly interested in monitoring the percentage of participants switching from no AED to AED treatment to determine the likely impact on power for the primary analysis.

Formal interim analyses of the accumulating data will be performed at regular intervals (at least annually) for review by an IDSMC. These analyses will be performed at the CTRC. The IDSMC will be asked to give advice on whether the accumulated data from the trial, together with results from other relevant trials, justifies continuing recruitment of further participants or further follow-up. A decision to discontinue recruitment, in all participants or in selected subgroups will be made only if the result is likely to convince a broad range of clinicians including participants in the trial and the general clinical community.

## 11.5 Analysis Plan

All primary analyses will be on an ITT basis including all randomised participants retained in their randomised treatment groups. Secondary compliance adjusted causal effect analyses will also be undertaken to assess the robustness of ITT analyses.

### 11.5.1 Primary and Secondary Outcomes

The primary outcomes are time to 6-month remission from seizures (for the hypothesis that carbamazepine or levetiracetam are superior to no AED) and change in CSHQ at 3 months (for the hypothesis that sleep behaviour intervention will be superior to standard care).

Following the principles discussed by Montgomery *et al.* (32), two separate regression analyses, one for each primary outcome, will be undertaken.

The interval (in days) from randomisation to occurrence of a 6-month remission will be summarised by Kaplan-Meier curves for each treatment group. A Cox proportional hazards model will be fitted with factors included for AED (CBZ, LEV vs no AED); sleep (intervention vs no intervention); baseline variables. The adjusted Hazard Ratio main effects of CBZ or LEV compared to no AED will be estimated and presented with a p-value and 95% confidence interval.

For the second primary outcome CSHQ, a linear regression model will be fitted with factors included for AED (CBZ, LEV vs no AED); sleep (intervention vs no intervention); baseline variables, including baseline CSHQ. The adjusted mean difference main effect of sleep intervention compared to no sleep intervention will be estimated and presented with a 95% confidence interval.

The impact of centre effect on the treatment comparison will be investigated by considering both fixed and random effects models. When analysing the data using the fixed effect approach, the centre effect is to be modelled by a series of dummy variables. However, due to concern regarding the number of dummy variables required, a random effects analysis will also be considered.

The primary analysis will address the principal research question focusing on treatment main effects. In secondary analyses the interaction between AED and sleep intervention will be investigated, recognizing that the precision of the estimates of interaction is very likely to be too poor for large effects to be ruled out.

All analyses will be reported in accordance with the CONSORT checklist (33) and regardless of statistical significance. There will be no correction for multiple comparisons (34).

A similar strategy will be used for the analysis of secondary time to event outcomes. For time to treatment failure, further analysis will be undertaken to assess the two main reasons for treatment failure - inadequate seizure control and unacceptable adverse effects. To allow for possible dependence between the different withdrawal risks, cumulative incidence analyses will be presented (34).

The Haybittle-Peto approach will be employed for each interim analysis, with 99.9% confidence intervals calculated for interim analysis effect estimates. The final analysis will be undertaken at the end of the trial when all participants have a minimum 12 months follow-up data and 95% confidence intervals will be calculated.

QOL data will be analysed longitudinally to explore between treatments changes in scale scores over time, taking account of baseline QOL.

Qualitative interview data will be analysed using an interpretive, reflexive and conceptual analytical approach. Data will be thematically analysed in discrete sets (e.g., the trial group and the non-trial groups, different treatments/management, different responses/experiences), and parents/primary carers' and children's transcripts will be analysed separately before considering each dyad and prior to synthesis of all the data.

For the analysis of safety events, all participants who received any amount of each trial drug will be included in the safety analysis dataset in the treatment group they actually received. All safety events reported by the clinical investigators will be presented, identified by treatment group. Safety events will be grouped according to a pre-specified coding system and tabulated. The number (and percentage) of participants experiencing each safety event, and the number (and percentage) of occurrences of each safety event will be presented. No formal statistical testing will be undertaken.

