#### *Practice*

Carbamazepine, a first-generation AED, is the current NICE standard treatment for RE (7). Our national survey confirmed that UK paediatricians prescribed carbamazepine as first-line choice (80%),

although there was great variability of choice amongst the remainder (8). Importantly, the survey revealed that in 40% of cases paediatricians treat RE patients conservatively, i.e. without drugs, as advocated in older textbooks (8). Carbamazepine has never been compared against no-treatment in RE, and in view of the AED's known cognitive adverse effects, it is important to know whether any benefit in terms of seizure control offsets its impact on children's learning. Second-generation AEDs (levetiracetam, lamotrigine, gabapentin, but not topiramate) have fewer cognitive side-effects in healthy adult volunteers than first-generation (carbamazepine, oxcarbazepine, valproate, phenobarbital, phenytoin) (9-15); and the International League Against Epilepsy judges only levetiracetam, of these second-generation AEDs, to have potential efficacy in RE (4). A generic version of levetiracetam was released in 2014 with comparable treatment cost to carbamazepine. Although not licensed for monotherapy in children, it is in widespread off-label use and is judged to be efficacious and well-tolerated (16). Thus levetiracetam would make an ideal and potentially superior comparator and has not been assessed head-to-head with carbamazepine in childhood epilepsy. NICE also made a specific research recommendation ([CG137:4.1]) for "levetiracetam to be evaluated as a first-line monotherapy in a prospective RCT [...] including *quality-of-life and cognitive outcomes*". The trial would complement the ongoing HTA-funded Standard and New Antiepileptic Drugs (SANAD-II) trial of levetiracetam, zonisamide and lamotrigine (Arm A: focal seizures), which has principally recruited adults (<http://www.nets.nihr.ac.uk/projects/hta/0914409>). The economic evaluation will address uncertainties and gaps in the evidence with respect to determining which interventions are cost-effective for use in practice and for broader adoption by the NHS.

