## 3.3 Objectives and Outcome Measures/Endpoints

Table 1: Summary of Objectives, Outcome Measures and Timepoints

| Primary Objectives                                                                                                               | Outcome Measures                                          | Timepoint(s) of evaluation of this outcome measure                                   |
|----------------------------------------------------------------------------------------------------------------------------------|-----------------------------------------------------------|--------------------------------------------------------------------------------------|
| To determine if carbamazepine or levetiracetam are superior to no AED with respect to time to 6-month seizure remission.         | Time to 6-month seizure remission based on seizure report | 3, 6, 12 months and annually thereafter - 'when was last seizure' question in clinic |
| To determine if a PBS intervention is superior to standard care with respect to 3-month sleep problem frequency measured by CSHQ | Total sleep problem score as measured by the CSHQ         | At baseline and 3 months                                                             |
| Primary Economic Objective †                                                                                          | Outcome Measures                                          | Timepoint(s) of evaluation of this outcome measure                                   |
| To estimate the cost-utility of carbamazepine, levetiracetam and PBS                                                             | Total costs; and quality-adjusted life years (QALYs)      | Resource use and utility questionnaires at baseline, 3, 12 months and annually       |

† This has no implications for sample size calculation

|                                                                                                          |                                                                                                                                                                                     | thereafter; routine hospital data at the end of the trial                        |

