## **7.5 Randomisation Procedures**

Patients **should not** be randomised until:

- a) Written informed consent has been obtained from an appropriate adult and assent if appropriate obtained from the patient;
- b) All eligibility criteria have been fulfilled and full eligibility has been confirmed by a medically qualified doctor and this has been recorded in the patient's medical notes and on the Eligibility case report form (CRF);
- c) The Baseline CRF has been completed.

All participants will be randomised firstly between carbamazepine or levetiracetam or active monitoring in a 1:1:1 ratio, and secondly between PBS or standard care in a 1:1 ratio (see flow diagram, Figure 1). A subset of participants will be purposively selected to wear an actigraphy watch and participate in the actigraphy sleep monitoring component.

If allocated to carbamazepine or levetiracetam, the randomised treatment should ideally begin on the day of randomisation, or within 14 days of randomisation at the latest. If the participant has been selected to wear an actigraph, the treatment should not commence until the actigraph has been worn for the first week (however treatment should still commence within the 14 day window after randomisation). Carbamazepine or levetiracetam treatment should be sourced via usual NHS arrangements (see section 9).

Participants will be randomised using a secure (24-hour) web-based randomisation programme. Allocation sequences will be computer-generated, and concealed from staff recruiting participants to the trial using a secure internet-based system created and maintained by the CTRC. A personal login username and password, provided by the CTRC, will be required to access the randomisation system; designated research staff will be issued with their personal login and password upon completion of training in the use of the system.

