### 11.3 Sample Size calculation

#### 11.3.1 Drug Intervention

The primary outcome is time to 6-month seizure remission. A 5% two-sided significance level is used for each of two primary comparisons of interest: carbamazepine versus active monitoring and levetiracetam versus active monitoring. We have obtained individual patient data from the trial sponsor of the German HEAD study (30) to provide an estimated probability of being without remission on placebo at 6 months of 0.57. With 97 per group we would have 80% power to detect a reduction from 0.57 to 0.37 (Hazard Ratio=0.57). Inflating sample size to allow for 12% attrition requires total n=330.

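### For failure due to unacceptable adverse reactions, the planned hazard ratios against no AED have no on-allocation control events to estimate from; levetiracetam versus carbamazepine is the contrast that fits

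*Protocol*

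**What the plan says.** The primary drug objective in section 3.3 is "To determine if carbamazepine or levetiracetam are superior to no AED with respect to time to 6-month seizure remission". Section 11.3.1 sizes the trial for it: "A 5% two-sided significance level is used for each of two primary comparisons of interest: carbamazepine versus active monitoring and levetiracetam versus active monitoring". Section 11.5.1 fits a Cox model with a three-level AED factor and states that "The adjusted Hazard Ratio main effects of CBZ or LEV compared to no AED will be estimated". For the other time-to-event endpoints it adds: "A similar strategy will be used for the analysis of secondary time to event outcomes". For the two reasons for treatment failure it also promises cumulative incidence analyses.

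One of those endpoints (section 2 and Table 1 in section 3.3) is time to treatment failure due to unacceptable adverse reactions. Three other places determine who can have that event:

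- Section 2 defines the drug control as active monitoring without an AED.
- Section 8.2.1 records the date and reason for failure of the randomised AED.
- Section 10.1 defines an adverse reaction as a response to a trial drug, related to a dose given to that participant.

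Section 3.2 (Practice) supports the choice of levetiracetam partly because it "has not been assessed head-to-head with carbamazepine in childhood epilepsy". No section names a levetiracetam versus carbamazepine contrast for a seizure or treatment-failure outcome.

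**The concern.** A contrast that suits remission is carried to an outcome that only two of the three arms can have while on allocation. The protocol says it will compare groups on this outcome, yet the only drug contrasts it states set each drug against an arm where the event is undefined on allocation.

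If the text is followed, the report will show either a model that does not converge to a finite hazard ratio, or a ratio driven by the few monitoring children who later started an AED. Neither says which drug is abandoned more often for intolerance. That question bears directly on the choice between the drugs, and the randomised data can address it.

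**Working it through.** **1. The plan's own sample size.** Inputs from section 11.3.1: 0.57 and 0.37 without remission at 6 months, two-sided 5%, 80% power. With the pooled-variance formula for two proportions (mean 0.47):

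n = [1.96·√(2·0.47·0.53) + 0.842·√(0.57·0.43 + 0.37·0.63)]² / 0.20² = (1.383 + 0.582)² / 0.04 ≈ 96.6, so 97 per group.

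This matches "With 97 per group we would have 80% power to detect a reduction from 0.57 to 0.37 (Hazard Ratio=0.57". The hazard ratio is ln 0.57 / ln 0.37 = 0.565. It is no AED relative to drug; drug relative to no AED is 1/0.565 = 1.77. For attrition, 3 × 97 / 0.88 = 330.7, in line with "Inflating sample size to allow for 12% attrition requires total n=330". The plan's figures therefore reproduce, and they refer to the two contrasts with no AED only.

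**2. Who can have an adverse-reaction failure.**

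| Arm | Randomised AED that can fail (8.2.1) | Trial-drug dose on allocation (10.1) | Event possible on allocation |
|---|---|---|---|
| Carbamazepine | yes | yes | yes |
| Levetiracetam | yes | yes | yes |
| Active monitoring | no | no | no |

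The sleep intervention does not alter this, because adverse reactions are defined by the two drugs alone. A monitoring child could contribute an event only after switching to an AED. Section 11.4 expects some switching, but under 8.2.1 such a child still has no randomised AED whose failure could be recorded.

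**3. What the Cox model does.** Take one drug against no AED, with n₁ and n₀ children at risk and no control events. Each drug-arm event contributes

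e^β / (n₁e^β + n₀) = 1 / (n₁ + n₀e^(−β))

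to the partial likelihood. This rises with β without reaching a maximum, so the estimated hazard ratio is infinite. If a few switchers do count as events, the estimate is finite but its size is set by how many children switched and to what. With the three-level factor, both drug coefficients diverge together while their difference, levetiracetam minus carbamazepine, remains estimable.

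**4. Precision of levetiracetam versus carbamazepine.** The drug arms are of equal size by design ("randomised firstly between carbamazepine or levetiracetam or active monitoring in a 1:1:1 ratio"). The protocol gives no assumed difference between the drugs, so the following are assumptions: 97 evaluable per arm and 1 − 0.37 = 63% reaching remission on both drugs.

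- Events: 2 × 97 × 0.63 = 122.
- SE(log HR) = 2/√122 = 0.181; CI factor exp(1.96 × 0.181) = 1.43.
- Hazard ratio detectable with 80% power: exp(−(1.96 + 0.842) × 0.181) = 0.60.

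Follow-up beyond 6 months would raise the remission fraction. At 90% there are 2 × 97 × 0.90 = 175 events, the CI factor is 1.35 and the detectable hazard ratio is about 0.65. As proportions without remission, 0.37 versus 0.27 has about 32% power with 97 per arm (341 per arm needed for 80%), and 0.37 versus 0.22 about 63% (144 needed).

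These figures concern remission. The protocol gives no rate for adverse-reaction failure. With d such failures split evenly over the two drug arms, the CI factor is exp(1.96 × 2/√d), which is wider than 1.43 whenever d is below 122.

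**The case against.** The strongest reply is that the plan is coherent and the rest belongs to the SAP. The objective, sample size and primary model all name the same two contrasts. A similar strategy need not mean identical contrasts, the three-level factor already contains levetiracetam versus carbamazepine, and section 11.1 promises a full SAP, which is not shown here. Cumulative incidence by arm also stays well defined when one arm has no events.

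Much of this stands. Three stronger readings that a reader might infer are not supported:

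- That the head-to-head gap is the rationale. Section 3.2 equally says that carbamazepine has never been tested against no treatment in this condition, and the primary analysis addresses that.
- That the trial compares the drugs only with no AED. This is true of the stated time-to-event contrasts. Cognition, quality of life, behaviour and other secondary outcomes are compared across all treatment groups, safety events are tabulated by group, and the economic evaluation covers every option.
- That any later head-to-head result must be post hoc. The SAP may specify it.

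What does not stand is the claim that nothing remains. The protocol makes a positive statement about the strategy for the secondary time-to-event outcomes, and the only drug contrasts in that strategy do not fit this one. Cumulative incidence curves display the drugs side by side but supply no estimated contrast between them. The safety tables carry no formal test.

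**Conclusion.** The point holds for time to failure due to unacceptable adverse reactions. Expected on-allocation events in the no-AED arm are zero by definition, so the inherited hazard ratios are not finitely estimable, or depend entirely on switchers. Levetiracetam versus carbamazepine is the only between-arm contrast with on-allocation events on both sides. This conclusion rests on the wording of sections 2, 8.2.1 and 10.1 and on no numerical assumption.

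The primary contrasts are correct as written. Naming levetiracetam versus carbamazepine for the seizure and other failure outcomes is a modest improvement rather than the repair of an error, justified because the head-to-head gap is part of the rationale. Its precision is limited: for remission, a CI of about ×/÷ 1.43 to 1.35 and 80% power only for a hazard ratio of about 0.60 to 0.65 or more extreme, under the assumed 63% to 90% remission on both drugs. It should be reported as an estimate, and a wide interval should not be read as equivalence. Overall importance is minor.

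**What to change.** Leave the primary contrasts as they are. After the sentence in section 11.5.1 that extends the strategy to the secondary time-to-event outcomes, add:

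1. For failure due to unacceptable adverse reactions, the comparison is levetiracetam versus carbamazepine, given as a hazard ratio with 95% CI and cumulative incidence by arm. Fitting it on the two drug arms avoids the divergent coefficients.
2. For the seizure and other treatment-failure outcomes, levetiracetam versus carbamazepine is also estimated from the same fitted models, as a pre-specified secondary contrast with a 95% CI and no power claim.

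The cost is two sentences. Sample size, data collection and primary models are unchanged. The downside is one further secondary comparison, uncorrected under the existing no-adjustment policy and of modest power, which the secondary label makes plain.

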### **11.5.2 Health Economic Evaluation**

The primary (cost utility) analysis will consider (patient) QALYs and costs from the perspective of the NHS and PSS. The incremental analysis will be based on the mean costs and QALYs for each treatment group, taking into consideration the factorial trial design (35). The Health Economic Analysis Plan (HEAP) (agreed prior to the analysis and produced by Bangor University), will define the analytic steps to be undertaken. Bangor University will impute data assumed missing at random using multiple imputation by chained equations as will be specified in the HEAP.

Sensitivity analyses will be conducted to test the robustness of findings. Bangor University will use such analyses based on the observed distributions of outcome and costs to test whether, and to what extent, the incremental cost-effectiveness ratios are sensitive to key assumptions in the analysis (e.g. unit prices, different utility estimates CHU-9D vs. EQ-5D-Y).

Bangor University will present alternative scenarios broadening the cost perspective, and considering a range of outcomes, including parental QALYs. These will be presented in a cost consequence analysis, and include indirect costs, such as educational attainment and loss of productivity, which will be valued by reference to published sources. Inclusion of spill-over disutility (impact on parents/primary carers' utility) will be based on the NICE reference case specification that all QALYs being of equal weight, and calculated assuming additive effects.

The joint uncertainty in costs and QALYs will be addressed through application of bootstrapping and estimation of cost-effectiveness acceptability curves (36). The cost-effectiveness frontier will allow for graphical representation of the interventions most likely to be cost-effective according to different thresholds of cost-effectiveness. The economic findings will be reported according to the CHEERS guideline (37).

